**Methods:**

A parallel, three-arm, stratified, cluster-randomized controlled trial design is being employed to evaluate intervention effects on institutional births, which is the primary outcome. Trial arms are: (1) upgraded MWH + religious/community leader training; (2) leader training alone; and (3) standard care. Twenty-four primary health care unit catchment areas (clusters) have been randomized and 3840 women of reproductive age who had a pregnancy outcome (livebirth, stillbirth or abortion) are being randomly recruited for each survey round. Outcome assessments will be made using repeat cross-sectional surveys at baseline and 24 months postintervention. An intention to treat approach will be used and the primary outcome analysed using generalized linear mixed models with a random effect for cluster and time. A cost-effectiveness analysis will also be conducted from a societal perspective.

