### Sample size

Methods outlined by Hooper and Bourke [22] for parallel-arm, cluster-randomized trials with repeated cross-sections were used to calculate the sample size (see Additional file 1). Briefly, the methodology requires calculation of two design effects, with the product of the two used to inflate the sample size under individual randomization to account for within-period intracluster correlation coefficient (ICC) and the between-period ICC. The within-period ICC is the correlation between any two women in the same cluster and the same period, while the between-period ICC is the correlation between any two women in the same cluster but different periods.

The first design effect (d_c_) due to cluster randomization was calculated using a within-period ICC of 0.1 obtained from a review of community-based, cluster-randomized controlled trials in low-resource settings focusing on maternal health-care service outcomes [23]. The design effect was calculated as:
$$ {\mathrm{d}}_{\mathrm{c}}=1+\left(\mathrm{m}-1\right)\uprho $$where m is the cluster-period size (i.e. the number of women surveyed per PHCU in each round) and ρ is the within-period ICC.

The second design effect (d_r_) due to repeated assessments (baseline and endline) was calculated using both the within-period ICC and a cluster autocorrelation coefficient (π) of 0.8 to allow for a 20% decay of the correlation from within to between different periods [22]. We had no prior information to inform the cluster autocorrelation coefficient, but a 20% decay was considered reasonable. The second design effect was calculated as:
$$ {\mathrm{d}}_{\mathrm{r}}=\left(1-{\mathrm{r}}^2\right) $$where r = (mρπ)/d_c_.

The sample size assuming individual randomization was then multiplied by both design effects to arrive at a required sample size of eight PHCUs per arm with an average of 160 women per PHCU per round of survey, for a total sample size of 3840 for each survey (total women recruited = 7680). This sample size achieves 80% power to detect an absolute difference in the proportions of institutional births of 0.17 assuming a control arm proportion of 0.4 and using a two-sided alpha of 0.025 to account for two pairwise comparisons. The control arm proportion was obtained from JZHO data. An absolute difference of 0.17 is the smallest difference that can be detected, i.e. the difference between the weakest intervention (hypothesized to be the leader training intervention) arm versus control.

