### Primary analysis: effectiveness of the intervention components

Baseline characteristics of women will be tabulated by trial arm to provide an overview of the study population and to check for any notable imbalances. Characteristics of interest will include the age of women, the education levels of women, the distance between home and the nearest health centre, and household wealth. Means, standard deviations and ranges will be presented for continuous variables, while frequencies and percentages will be reported for categorical variables.

An intention to treat approach will be employed where random assignments of clusters to the three trial arms will be preserved regardless of adherence to the intervention assignment. The primary outcome will be analysed using a generalized linear mixed model with random effects for PHCU (cluster) and time, and fixed effects for time, time by trial arm interaction, and the stratification variables. The main effects for trial arm will be dropped to constrain differences between the arms at baseline as recommended by Hooper et al. [24]. With only two measurement points, it will not be possible to determine whether or not time has a more complex relationship with the outcome (quadratic or cubic) and therefore only a first-order term for time will be included. To account for the bias due to a small number of clusters, we will use the Kenward–Roger degrees of freedom approximation [25].

A logit link function will be used, and the outcome assumed to have a binomial distribution. Pairwise comparisons of adjusted least square mean differences will be made together with 97.5% confidence intervals to determine the effect of each intervention arm versus control.

Odds ratios will be calculated by taking the exponential of the relevant combinations of regression coefficients. The ICC and cluster autocorrelation coefficient for institutional births (primary outcome), antenatal care use, and postnatal care use will be calculated in STATA and reported on the proportions scale. Secondary outcomes will be analysed as described for the primary outcome.

Statistical tests and confidence intervals will be two-sided; between-group comparisons will be calculated and presented with 95% confidence intervals with the significance levels set at the 2.5% level.

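### The primary model names random effects for PHCU and time but no PHCU-by-time effect; fitted literally, it contradicts the sample-size autocorrelation of 0.8 and would roughly halve the standard errors

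*Protocol article*

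**What the plan says.** Under Primary analysis, the protocol article gives a logit-link mixed model and lists its terms as follows: "random effects for PHCU (cluster) and time, and fixed effects for time, time by trial arm interaction, and the stratification variables". Arm main effects are dropped so that the arms share a common baseline, and Kenward–Roger degrees of freedom are to be used because clusters are few. The same section says that the ICC and the cluster autocorrelation coefficient will be reported for institutional births, antenatal care and postnatal care. Secondary outcomes follow the primary model.

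The abstract words the random part differently, with a singular effect: "generalized linear mixed models with a random effect for cluster and time".

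The Sample size section defines a within-period and a between-period ICC. The first design effect "was calculated using a within-period ICC of 0.1 obtained from a review". The second uses an autocorrelation "of 0.8 to allow for a 20% decay of the correlation from within to between different periods". The authors add: "We had no prior information to inform the cluster autocorrelation coefficient, but a 20% decay was considered reasonable".

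**The concern.** Time is listed as both a fixed and a random effect. With two rounds and a fixed time effect, a random time effect common to all PHCUs has no identifiable variance. It shifts every PHCU equally within a round, so it also drops out of any contrast between arms. What remains is a PHCU intercept, which assumes that each PHCU's underlying rate moves between rounds only by the common time trend and the arm effect.

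An autocorrelation of 0.8 says otherwise: one fifth of the between-PHCU variance is specific to the round. The arm effect is largely a contrast of PHCU-level change, so this is the variance that matters most. If it is omitted, 160 women per PHCU-round count as almost independent information on that change, and confidence intervals are too narrow. Kenward–Roger adjusts for uncertainty in the variance components that are in the model; it does not supply one that is absent. A model with the autocorrelation fixed at 1 also cannot yield the autocorrelation that the plan promises to report.

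**Working it through.** **Inputs (Sample size section).** Within-period ICC ρ = 0.1; autocorrelation π = 0.8; m = 160 women per PHCU per round; 8 PHCUs per arm; 0.40 versus 0.57; two-sided alpha 0.025 per comparison (critical value 2.2414); 80% power.

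**1. The plan's own figure.**
- d_c = 1 + 159 × 0.1 = 16.9.
- r = 160 × 0.1 × 0.8 / 16.9 = 0.757; d_r = 1 − r² = 0.426.
- d_c × d_r = 7.205.
- The pooled two-proportion formula gives 163 women per arm under individual randomization. 163 × 7.205 ≈ 1174, and 1174 / 160 = 7.34 PHCUs, rounded up to 8.

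The stated "required sample size of eight PHCUs per arm with an average of 160 women per PHCU per round of survey" reproduces, and it relies on the 0.8.

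**2. Variance components implied by the plan** (linear scale, total variance 1). PHCU 0.1 × 0.8 = 0.08; PHCU-by-round 0.1 − 0.08 = 0.02; residual 0.90.

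**3. Standard error with the PHCU-by-round term** (common baseline, one arm versus control).
- Variance of a PHCU-round mean: V = 0.08 + 0.02 + 0.90/160 = 0.1056.
- Correlation between rounds: 0.08 / 0.1056 = 0.757, the same r as in the plan's formula.
- SE = √[V(1 − r²) × 2/8] = √[0.1056 × 0.4264 × 0.25] = 0.106.

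**4. Standard error that the intercept-only model reports.** The omitted 0.02 is absorbed by the two components that remain.
- Residual: (318 × 0.90 + 160 × 0.02 + 0.90) / 319 = 0.910.
- PHCU: 0.08 + 0.01 + 0.90/320 − 0.910/320 = 0.090.
- The model therefore believes V′ = 0.090 + 0.910/160 = 0.0957 and r′ = 0.090 / 0.0957 ≈ 0.9405.
- Reported SE = √[0.0957 × (1 − 0.9405²) × 0.25] = 0.0525.

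**5. True standard error of that model's estimate** (it weights baseline by r′).
- √[(V(1 + r′²) − 2r′ × 0.08) × 0.25] = 0.110.
- Ratio 0.0525 / 0.110 = 0.48 (0.50 against the 0.106 of step 3).

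**6. Type I error.** 2 × [1 − Φ(2.2414 × 0.477)] = 0.285; with a t reference on 21 df, 0.263. The nominal level is 0.025.

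**7. Check on the logit scale.** Null trials were simulated with 24 PHCUs, two rounds and 160 women each. The logit-scale variance was 0.508 (ICC 0.1 at a proportion of 0.4), split 80/20 between PHCU and PHCU-by-round.

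| Fitted model | Trials | Mean SE | Empirical SD | Rejection at nominal 2.5% |
|---|---|---|---|---|
| PHCU only | 380 | 0.118 | 0.238 | 25% (z) |
| PHCU + PHCU-by-round | 380 | 0.223 | 0.229 | 3.6% (z) |

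A separate set of 1,600 null trials gave about 27% (z) or 23% (t, 20 df) for the first model, and about 5% (z) or 3.6% (t, 20 df) for the second. The 380-trial run omitted the strata. Kenward–Roger was not applied in these figures.

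**8. Sensitivity of the literal reading** (formulas of steps 4–6, normal reference).

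| ICC | Autocorrelation | Reported / true SE | Type I error |
|---|---|---|---|
| 0.02 | 0.8 | 0.80 | 7% |
| 0.05 | 0.8 | 0.62 | 16% |
| 0.10 | 0.8 | 0.48 | 29% |
| 0.15 | 0.8 | 0.39 | 38% |
| 0.10 | 0.6 | 0.36 | 42% |
| 0.10 | 0.9 | 0.61 | 17% |
| 0.10 | 1.0 | 1.00 | 2.5% |

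**The case against.** The strongest reply is that the sentence is loose rather than wrong. The random effects for PHCU and time can be shorthand for a PHCU intercept plus a time effect that varies within PHCU. Under that reading the decay is modelled and the standard errors are about right (ratio 0.97 in the simulation). Three things favour it. A random main effect of time beside a fixed one would do no work, so the authors are unlikely to have meant it. The promised autocorrelation needs a cluster-period component. The sample size is built on separate within- and between-period ICCs. The article is also a condensed document, and an analysis plan not shown may give the exact structure.

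Most of this stands. A reader might infer that the trial will ignore the decay and will report standard errors of half the proper size. The documents do not support that as a certainty: it follows only under the literal reading, and only at ICC 0.1 with autocorrelation 0.8. The first value comes from a review of other trials and the second had no prior data behind it.

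The reply does not remove the point. The article does not leave the random structure open; it states one, and that statement conflicts with the Sample size section and with the planned autocorrelation report. The intended model has to be inferred against the sentence that defines the primary analysis, and the abstract's singular effect adds to the ambiguity. Lack of prior information on the autocorrelation is a reason to estimate it, not to fix it at 1.

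**Conclusion.** The point holds in conditional form. As literally written, the primary model reduces to a PHCU intercept and contradicts the plan's own autocorrelation of 0.8. If it were fitted that way at the design values, reported standard errors would be about half their true size and type I error about 23–29%. The direction is the same for any autocorrelation below 1; the size varies as tabulated and vanishes at 1. A cluster-period term was probably intended, so this is a defect in the stated model, not evidence that a wrong analysis will be run. It should still be corrected, because the primary inference depends on which model is fitted. The number of clusters is unaffected: 8 per arm reproduces.

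**What to change.** Replace the random-effects sentence with: random effects for PHCU and for PHCU-by-time (cluster-period); fixed effects for time, time-by-arm and the strata. Delete the random main effect of time and align the abstract. State that the secondary outcomes use the same structure, and that the reported ICC and cluster autocorrelation are derived from it.

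The cost is one sentence and one more variance component in the code, with no new data and no change in sample size. Intervals will be wider than the literal model would give, but they will match the assumptions on which the trial was sized.

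### The primary analysis section gives two confidence levels, 97.5% and 95%, for the same between-arm comparisons, and only the 97.5% interval matches the planned two-sided 2.5% test

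*Protocol article*

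**What the plan says.** Three statements in the protocol article bear on the point.

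- **Sample size section.** The trial is sized "using a two-sided alpha of 0.025 to account for two pairwise comparisons", that is, 0.05 split equally over the two comparisons with control.
- **Primary analysis section, paragraph on the logit link.** "Pairwise comparisons of adjusted least square mean differences will be made together with 97.5% confidence intervals", for the effect of each intervention arm against control.
- **Primary analysis section, closing sentence.** "Statistical tests and confidence intervals will be two-sided", and "between-group comparisons will be calculated and presented with 95% confidence intervals with the significance levels set at the 2.5% level".

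The same section also states: "Secondary outcomes will be analysed as described for the primary outcome".

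**The concern.** A comparison of an intervention arm with control is a between-group comparison, so the second and third statements both govern the primary result and cannot both be followed. The closing sentence also does not fit together on its own terms. The interval that corresponds to a two-sided test at level a is the 1 − a interval, so a 2.5% test goes with a 97.5% interval and a 95% interval goes with a 5% test.

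At stake is how the primary result is reported and read. For any p-value between 0.025 and 0.05, a 95% interval would exclude no effect while the planned test is non-significant. The article says that the results are meant for policy makers deciding on scale-up, who may well read the interval rather than the p-value. With both levels written down, either interval could also be reported with the protocol as authority.

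**Working it through.** **Inputs.** From the sample size section: control proportion 0.40 and difference 0.17, hence 0.57 in the intervention arm; 80% power; two-sided alpha 0.025; within-period ICC 0.1; cluster autocorrelation 0.8; 8 clusters per arm; 160 women per cluster per round. Assumed here: degrees of freedom, because the article names the Kenward–Roger approximation but gives no value. I use 14 (16 clusters in one contrast, less 2), 21 (24 clusters, less 3) and the normal limit. Also assumed: correlation 0.5 between the two test statistics, from the shared control and equal arms.

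**1. Which alpha the design was sized for.**

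- d_c = 1 + (160 − 1) × 0.1 = 16.9
- r = 160 × 0.1 × 0.8 / 16.9 = 0.757, so d_r = 1 − r² = 0.4264
- Product of the design effects = 7.205

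The first two columns give the range without and with continuity correction for two proportions.

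| Two-sided alpha | Individually randomized n per arm | × 7.205 | Clusters of 160, rounded up |
|---|---|---|---|
| 0.025 | 163 to 175 | 1174 to 1261 | 7.34 to 7.88, so 8 |
| 0.05 | 135 to 147 | 973 to 1059 | 6.08 to 6.62, so 7 |

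The stated design of 8 × 160 = 1280 per arm per survey is reproduced at two-sided 0.025 and not at 0.05. The split alpha is therefore what the trial was built on.

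**2. Width of the two intervals.** The ratio of critical values, 97.5% to 95%, is:

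- normal limit: 2.241 / 1.960 = 1.14
- 21 df: 2.414 / 2.080 = 1.16
- 14 df: 2.510 / 2.145 = 1.17

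**3. Chance of a discordant result (p between 0.025 and 0.05).** Under no effect it is 0.05 − 0.025 = 2.5% per comparison. At the design difference:

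- Effective n per arm = 1280 / 7.205 = 177.6
- SE = √[(0.40 × 0.60 + 0.57 × 0.43) / 177.6] = √(0.4851 / 177.6) = 0.0523
- Noncentrality = 0.17 / 0.0523 = 3.25
- Normal limit: Φ(2.241 − 3.253) − Φ(1.960 − 3.253) = 5.8%
- Noncentral t: 8.1% at 21 df and 9.4% at 14 df

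This SE is on the risk-difference scale that the sample size uses. The planned analysis is on the logit scale, so the figures are approximate.

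**4. Family-wise error over the two comparisons, both null.** From the bivariate normal with correlation 0.5:

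- both read from 95% intervals, |z| > 1.960: 9.1%
- both read from 97.5% intervals, |z| > 2.241: 4.6%

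With independent statistics these would be 1 − 0.95² = 9.75% and 1 − 0.975² = 4.94%.

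**The case against.** The strongest defence is that the decision rule is not in conflict. The sample size section and the closing sentence of the analysis section both put the test at 2.5%, and nothing says that a 95% interval decides significance. This stands. A reader might infer that the plan itself carries a family-wise error of about 9%. The documents do not support that: as written, the Bonferroni bound of 2 × 0.025 = 0.05 holds, and the 9.1% arises only if someone sets aside the stated level and judges by 95% intervals.

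A second defence is that the specific sentence on arm-versus-control contrasts takes precedence over a general reporting line, so the primary result would receive its 97.5% interval. This is plausible but not secured by the text. The closing sentence is in the primary analysis section, carries no restriction, and its wording covers those same contrasts. Confining the 95% level to secondary outcomes fails as well, because those are to be analysed in the same way as the primary.

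A third reading takes 2.5% as the tail area on each side of a 95% interval. It fails because the sample size section calls 0.025 two-sided and ties it to the two comparisons.

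Finally, any single figure for the discordant zone depends on degrees of freedom that the article does not state. That is correct, and only the range should be quoted.

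**Conclusion.** The point holds as an inconsistency in the reported interval. Two confidence levels are given for the same comparisons, and the 95% level does not correspond to the two-sided 2.5% test. The test level, the control of type I error by that test, the model and the sample size are unaffected, so this should not be read as a flaw in the error control or the sizing of the trial.

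Per comparison, the interval and the test would disagree with probability about 6% to 9% at the design difference of 0.17. This rests on the plan's ICC, autocorrelation and cluster sizes, and on 14 degrees of freedom up to the normal limit. The family-wise figure of 9.1% against 4.6% describes a possible misreading and not the plan's operating characteristics.

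**What to change.** In the closing sentence of the primary analysis section, change the interval level from 95% to 97.5%. The sentence then agrees with its own 2.5% significance level, with the earlier sentence in the section and with the sample size section. It also applies equally to the secondary outcomes. If 95% intervals are shown as well, add that they are descriptive and not used to judge significance.

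The repair should not move secondary outcomes to 95% intervals. That would conflict with the statement that they are analysed as the primary outcome is, and would leave their 2.5% level without a matching interval.

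The cost is one number in one sentence. The reported intervals are about 14% to 17% wider than 95% intervals, which the alpha split already implies, and no additional women or clusters are needed. On the article's timeline the endline survey had not begun, so the change could be made before endline outcomes are seen.

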### Secondary analysis: understanding implementation for scale-up

Due to the pragmatic nature of the trial and an interest in supporting scale-up, if found to be effective, the RE-AIM framework is being used to guide secondary analyses focusing on implementation. Briefly, the impact of an intervention is assessed by evaluating reach, efficacy, adoption, implementation, and maintenance [26]. Reach and efficacy measures are captured in our primary and secondary trial outcomes; adoption, implementation and maintenance of the intervention components will be gauged using qualitative data collected from HEWs, health centre staff, and district and zonal health office staff. Uptake of the intervention components, changes in policy implementation and financial support as well as mechanisms used to sustain the interventions that develop during the trial will be examined. Finally, the short- and long-term cost-effectiveness of the intervention components will be determined using a decision analytic modelling approach. The short-term cost-effectiveness analysis will be based on trial data as well as data specific to the Jimma zone and Ethiopia. This short-term study will provide an incremental cost per intermediate outcomes, including the number of women who have institutional births. A Markov model will be developed and used to simulate the natural history of pregnancy, pregnancy-related complications, and the long-term cost-effectiveness of maternal and neonatal interventions of interest over the lifetime period of women. The outcomes of the long-term model will be expressed as an incremental cost per an additional life year saved. We will conduct extensive sensitivity analyses, including both deterministic and probabilistic sensitivity analysis with Monte-Carlo simulations, to assess the robustness of our model to parameter uncertainty. Where possible, we will utilize the regression analyses on baseline sociodemographic characteristics associated with cost and outcome and stratify the simulated cohort to reflect these sources of variability in cost-effectiveness outcomes.

## Ethics and dissemination

### Research ethics approval

Ethical approval was obtained from the University of Ottawa Health Sciences and Science Research Ethics Board (File no. H10–15-25B) and the Jimma University College of Health Sciences Institutional Review Board (Ref. no. RPGE/449/2016). Informed consent will be obtained from all study participants.

### Protocol amendments

The trial was initially designed with three rounds of survey, but due to budget constraints the protocol was changed to include only two surveys (baseline and endline). This was done after the baseline survey but prior to analysis. This resulted in the minimum absolute detectable difference increasing from 15% to 17% to maintain other sample size parameters (80% power, ICC = 0.1 and 24 clusters with 160 women each). An economic analysis component was also included (protocol version 3.0, January 2016) and consent forms simplified as per ethics board feedback (protocol version 2.0, October 2015).

